### Data Collection

For the primary outcomes, we will use the data collected for the Expect Study II. For the secondary outcomes, when comparing the effects of risk-dependent care with former care-as-usual, the outcomes of the Expect Study II will be compared with the outcomes of the Expect Study I. For this reason, the survey intervals and the questions regarding the secondary outcomes are similar between the two studies.

In the Expect Study II, data will be collected using the Expect prediction tool, comprising women’s personal risk profile, and Web-based patient surveys. A structured overview of patient enrolment and data collection for the Expect Study II is shown in Figure 1.

The first survey addresses the following topics: (1) recommendations and information given by health care professionals, (2) women’s intention to comply with these recommendations, (3) dietary intake of calcium and vitamin D and sunlight exposure, and (4) vitamin and mineral supplement usage.

The second and third surveys are comparable to each other and will address the following topics: (1) patient satisfaction, (2) women’s state anxiety, (3) maternal quality of life, (4) changes in vitamin and mineral supplement usage, and (5) health care resource use.

**Table 1 table1:** Overview of care pathways.

Gestational age (weeks)	Basic antenatal care for all women	Additional risk-dependent care				
		Pre-eclampsia (mildly elevated risk)	Pre-eclampsia (high risk)	Gestational diabetes mellitus	Small or large gestational age infancy	Spontaneous preterm birth
6-10	Intake and risk assessment using the Expect prediction tool and general recommendations (eg, Calcium and vitamin D intake)					
10-12	Confirmation gestational age (crown rump length ultrasound) and blood tests (eg, blood type, hemoglobin)	Low dose aspirin prophylaxis	Low dose aspirin prophylaxis and extended blood tests (eg, renal function)			Cervical length measurement
14			BP^a^ measurement			
16			BP measurement	OGTT^b^ (in case of history of GDM^c^)		Cervical length measurement and progesterone prophylaxis
18-20	Check-up (eg, BP and symphysio-fundal height measurements) and ultrasound screening for congenital abnormalities					Cervical length measurement
22			BP measurement			
24-26	Check-up		BP measurement	OGTT		Cervical length measurement
27	Additional blood tests (depending on Rhesus genotype)					
28			BP measurement and ultrasound fetal biometry	Ultrasound fetal biometry	Ultrasound fetal biometry	Cervical length measurement
30	anti-D immunoglobulin prophylaxis (depending on genotype)					
32	Check-up, blood tests (eg, hemoglobin), and ultrasound fetal biometry					Cervical length measurement
34			BP measurement			
36	Check up and ultrasound fetal biometry		Ultrasound fetal biometry		Ultrasound fetal biometry	
37			BP measurement			
38			BP measurement			
39			BP measurement			
40	Check-up and shared decision regarding induction of labor					
41-42	Check-up					

^a^BP: blood pressure.

^b^OGTT: oral glucose tolerance test according to the International Association of the Diabetes and Pregnancy Study Group's (IADPSG) criteria.

^c^GDM: gestational diabetes mellitus.

**Figure 1 figure1:**
[figure not shown]
Flowchart of participant enrolment and data collection of the Expect Study II. Whether or not a woman participates to the Expect Study II does not affect the health care women receive during their pregnancy.

In order to document the nature and volume of health care resource used, women will be asked to record all visits to midwives, hospitals, and other care institutions. Furthermore, questions related to medication use, hospital admission, diagnostic and medical procedures, and the delivery will be asked. To minimize patient recall problems, information regarding the usage of health care resources will be requested at three intervals (surveys two, three and four) during the study period.

Survey four, the postpartum survey, addresses obstetric outcomes, compliance of health care recommendations, and the topics mentioned in survey two and three. Furthermore, this survey also contains questions regarding the health care consumption related to the neonate.

### Sample size

According to the results of the validation study (Expect I) we expect approximately 30% of women to have an elevated estimated risk of PE, the obstetric complication with the lowest incidence (unpublished study submitted by [name] et al, January 2018). Furthermore, an adherence of 70% and a compliance of approximately 40% is expected for the recommended aspirin treatment. This will result in approximately 21% and 12% respectively of the general population having an elevated risk of PE. In order to estimate these percentages with a precision of approximately 4% the required sample size is estimated at 400 participants [18].

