### Outcome Measures and Measurement

The primary outcomes are health care professionals’ adherence to key recommendations and compliance of the women involved in the study. Adherence is defined as the proportion of women that actually received the key recommendations they should have received from their health care professional according to the LOC guidelines. Adherence will be analyzed regarding recommendations of adequate vitamin D (yes or no) and calcium intake (yes or no) for all women, preventive aspirin treatment (yes or no) for women with elevated PE risks, and OGTT (yes or no) for women with elevated GDM risks.

Compliance is defined as the proportion of women whom comply with the LOC recommendations they have received (yes, no or partially). Compliance will be analyzed regarding: adequate vitamin D (10 microgram per day) and calcium (1,000 milligram per day) intake, preventive aspirin treatment, and OGTT.

The secondary outcomes are patient satisfaction and cost-effectiveness. These secondary outcomes of Expect Study II will be compared to the outcomes of Expect Study I.

Patient satisfaction will be measured by validated patient satisfaction questionnaires. The Patient Satisfaction Questionnaire Short Form will be incorporated in antepartum surveys two and three. In the postpartum survey, patient satisfaction will be assessed by the Pregnancy and Childbirth Questionnaire (PCQ) [16]. The PCQ is validated for Dutch women who recently gave birth and addresses three topics: women’s satisfaction with the health care professional during pregnancy, health education, and satisfaction with the health care professional during labor. Furthermore, Truijens et al showed the PCQ is sensitive to pick up effects regarding patient satisfaction due to simulation-based obstetric team training [17].

In order to perform cost-effectiveness calculations, we will calculate two incremental cost-effectiveness ratios (ICERs). The first ICER expresses the health care costs per one neonatal composite outcome prevented. The neonatal composite outcome is defined as perinatal death within seven days after birth, asphyxia (Apgar score <7 after 5 minutes), admission to a neonatal intensive care unit within 28 days after birth, SGA (birthweight <2.3 weight percentile), and very preterm birth (birth before 32 completed weeks of pregnancy) [13]. The second ICER will express the health care cost per one maternal gained Quality Adjusted Life Year (QALY).

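### The stated precision of about 4% belongs to shares of all women, not to aspirin adherence and compliance as defined, where 400 women give about ±8 and ±10 points

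*Protocol article*

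**What the plan says.** The Sample size section of the protocol article starts from two planning assumptions: "we expect approximately 30% of women to have an elevated estimated risk of PE", and "an adherence of 70% and a compliance of approximately 40% is expected for the recommended aspirin treatment". It combines them as follows: "This will result in approximately 21% and 12% respectively of the general population having an elevated risk of PE". The sample size then follows: "In order to estimate these percentages with a precision of approximately 4% the required sample size is estimated at 400 participants".

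The outcomes themselves are defined under Outcome Measures and Measurement. "Adherence is defined as the proportion of women that actually received the key recommendations they should have received from their health care professional". For aspirin the relevant group is named: "preventive aspirin treatment (yes or no) for women with elevated PE risks". For the second outcome, "Compliance is defined as the proportion of women whom comply with the LOC recommendations they have received". The Statistical Analysis section repeats this denominator for compliance, namely women who received the recommendation.

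**The concern.** The sample-size paragraph and the outcome definitions concern different quantities. The paragraph gives a precision for two shares of the whole cohort. The primary outcomes are conditional proportions in subgroups that are much smaller than the cohort. No section names a whole-cohort share of adherent or compliant women as an outcome, so the only precision figure in the article describes something it does not say it will report.

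Two further faults sit in the same paragraph:

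- The 12% is 0.30 × 0.40, which takes compliance over all elevated-risk women. The definition takes it over advised women.
- The sentence describes 21% and 12% as the population share at elevated risk. They are the shares who are at elevated risk and also advised, or also compliant.

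A reader who takes the paragraph as the justification for the primary outcomes would expect aspirin adherence and compliance to be known to within about 4 points. The intervals that are reported will be two to two and a half times as wide.

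**Working it through.** **Inputs**

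- Sample size section: 30% at elevated risk, adherence 70%, compliance 40%, N = 400, precision about 4%.
- Outcome Measures and Measurement, and Statistical Analysis: the denominators.
- Assumption: the article states no confidence level. I read precision as the half-width of a two-sided 95% interval (z = 1.96), because that reproduces 400. At 90% the half-width for 21% would be 3.35 points.

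**Formulas**

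Half-width = z √(p(1 − p)/n), and n = z² p(1 − p)/d².

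**Step 1: reproduce the plan's figure (all participants as denominator)**

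- 0.30 × 0.70 = 0.21 and 0.30 × 0.40 = 0.12.
- n for 21% ± 4 points: 1.96² × 0.21 × 0.79 / 0.04² = 398.3, in effect the stated 400.
- n for 12% ± 4 points: 1.96² × 0.12 × 0.88 / 0.04² = 253.5, so the 21% drives the sample size.
- Half-widths at 400: 1.96 × √(0.21 × 0.79/400) = 3.99 points, and 1.96 × √(0.12 × 0.88/400) = 3.18 points.

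The arithmetic is right for these two quantities.

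**Step 2: denominators under the outcome definitions**

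- Women at elevated risk: 0.30 × 400 = 120 (aspirin adherence).
- Women advised: 120 × 0.70 = 84 (aspirin compliance).

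**Step 3: half-widths on those denominators**

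| Outcome | p | n | Half-width | Interval | Ratio to 4 points |
|---|---|---|---|---|---|
| Adherence | 70% | 120 | 1.96 × √(0.21/120) = 8.2 points | about 62–78% | 2.0 |
| Compliance, as defined | 40% | 84 | 1.96 × √(0.24/84) = 10.5 points | about 30–50% | 2.6 |
| Compliance over all at elevated risk | 40% | 120 | 1.96 × √(0.24/120) = 8.8 points | about 31–49% | 2.2 |

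Wilson intervals agree: 8.1, 10.3 and 8.6 points.

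**Step 4: the 12%**

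Under the stated definition, the share of all women who comply is 0.30 × 0.70 × 0.40 = 0.084, or 8.4%. If 12% of all women were compliers after all, compliance among the advised would be 0.12/0.21 = 57%, not 40%. Its half-width with 84 women would be 10.6 points.

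**Step 5: what ±4 points would take on the defined outcomes**

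- Adherence: 1.96² × 0.21/0.04² = 504.2 women at elevated risk. 504.2/0.30 is about 1,681 enrolled.
- Compliance: 1.96² × 0.24/0.04² = 576.2 women advised. 576.2/0.21 is about 2,744 enrolled.

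**The case against.** The best defence is that the paragraph is open about what it does. It converts to whole-population percentages and claims precision for those percentages, and for them the claim is correct. On this view the fault is not a wrong sum but the absence of a precision for the conditional proportions. The first part stands: the calculation is sound for 21% and 12%. It does not rescue the paragraph, which is the article's only precision statement for its primary outcomes and uses quantities that are not among them.

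Scope is a fair limit. Adherence to vitamin D and calcium advice applies to all women, and there 400 gives at most 1.96 × √(0.25/400) = 4.9 points. For the glucose tolerance test, the article gives no share of women at elevated risk, so nothing can be computed. The shortfall is shown for aspirin, which is the recommendation the study is sized on.

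The article does not say what the 40% is a proportion of. If it was meant over all elevated-risk women, 12% is a consistent planning figure. The conflict then moves to the outcome definition, and the half-width is still ±8.8 points.

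Finally, the primary outcomes are descriptive, with no test, margin or success threshold, and intervals of about 62–78% and 30–50% are still informative for an implementation study. That bears on how serious the point is. It does not make the stated figure right.

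**Conclusion.** The concern holds. The 4% precision is correct for 21% and 12% of all participants, but it does not apply to aspirin adherence and compliance as the article defines them. With 400 women, their half-widths are about ±8.2 and ±10.5 points. If compliance is taken over all elevated-risk women, its half-width is ±8.8. The 12% is inconsistent with the article's definition of compliance, and the description of 21% and 12% as shares at elevated risk is wrong on the paragraph's own 30%.

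These results rest on the article's planning values, on a 95% confidence level (assumed) and on complete responses. Missing answers would widen the intervals, by an amount the article gives no basis to compute. The error lies in a stated design figure. The outcome estimates would not change, and no decision threshold depends on the figure.

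**What to change.** Keep 400 and rewrite the end of the Sample size paragraph, for example:

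> With 400 women, about 120 are expected to have an elevated risk of pre-eclampsia, and about 84 of these to have been advised aspirin. The expected half-widths of the 95% confidence intervals are about 8 percentage points for adherence (70% of 120) and about 10 for compliance (40% of 84).

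Alongside this:

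- State what the 40% is a proportion of. If it is of advised women, replace 12% by 8.4%. If it is of all elevated-risk women, then either give compliance among the advised as 57% (±10.6 points), or change the compliance definition in Outcome Measures and Measurement and in Statistical Analysis and quote ±8.8. Keeping the present definition is simpler, since those two sections already agree and 300 of the 400 women are enrolled.
- Remove the statement that 21% and 12% are the shares at elevated risk.
- If uptake across the whole cohort is also of interest, name it as a separate measure. The ±4 points can stay attached to the 21%.

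The cost is wording only, with no extra participants. The price is a less favourable precision statement, best corrected before results are reported.

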### Statistical Analysis

Missing values will be handled by imputation. Stochastic regression imputation with predictive mean matching as the imputation model will be used to prevent biased results based on complete case analysis only [19].

Adherence will be calculated by the proportion of women who reported to have received the LOC recommendations regarding adequate vitamin D and calcium intake, preventive aspirin treatment, and OGTT. Answers of participants will be linked to their estimated risk profile based on the Expect prediction tool.

Compliance will be analyzed by calculating the proportion of women who complied with the recommendations received from their health care professional regarding aspirin treatment, OGTT, vitamin D, and calcium intake. Vitamin D is analyzed based on supplement intake and sunlight exposure. Calcium intake is determined by calculating the daily intake from diet and supplement use. Dietary intake will be estimated using answers from a selection of questions from the Dutch National Food Frequency Questionnaire tool [20]. These questions address food products that cumulatively cover >80% of the variance in calcium intake [21]. Total intake of both nutrients will be compared with the recommended intake by the LOC (1000 milligram calcium per day and 10 microgram of vitamin D per day) in order to determine compliance to these recommendations.

The secondary outcomes, patient satisfaction and cost-effectiveness, will be analyzed by comparing Expect Study II with the outcomes of former care-as-usual (Expect Study I). Patient satisfaction scores will be analyzed using multiple linear regression.

For the economic evaluation, we will use a health care perspective according to the Dutch guidelines for cost calculations [22]. A time horizon of approximately eleven months, from onset of pregnancy up to six weeks post-partum, will be applied. Maternal quality of life will be evaluated using the Euroqol EQ-5D-3L and EuroQol Visual Analogue Scale (EQ VAS) questions which are incorporated in the surveys. The EQ-5D-3L and EQ VAS are standardized questionnaires used worldwide to assess quality of life. Maternal QALYs will be calculated using the corresponding utility scores based on the Dutch population [23,24]. All costs will be expressed as 2017 Euros and if necessary cost prices will be transformed to 2017 Euros using the Dutch Consumer Price Index [25]. Bootstrap- and standard sensitivity analyses will be performed to quantify the uncertainty regarding the cost-effectiveness outcomes.

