The midwives and gynecologists play a central role in enrolling pregnant women into the Expect Study II, by asking women whether they are interested in receiving further information about participating in the Expect Study II. Almost every pregnant woman is eligible for our study. The exclusion criteria are (1) maternal age <18 years, (2) documented multiple pregnancy, and (3) ≥16 weeks of gestation at intake. The eligibility criteria are identical to those of the Expect Study I cohort [13]. Eligible women agreeing to participate are asked to give informed consent and to complete 4 Web-based surveys at enrolment, 24 weeks and 34 weeks of gestation, and 6 weeks after due date.

A personal link to the first online survey will be sent immediately after enrolment. If the survey was not accessed or incomplete, 2 automatic reminders will be sent by email at 3-day intervals for surveys one to three and at 6-day intervals for the postpartum survey. In case of non-response, women will be contacted by phone (provided that a correct phone number is available). If women report PTB at the beginning of survey two or three, they will automatically be redirected to the postpartum survey.

The medical ethical committee of Maastricht University Medical Centre evaluated the study protocol and declared that the study did not fall within the scope of the Dutch Medical Research Involving Human Subjects Act (WMO; METC-17-4-057).

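### The named imputation method is ordinarily single imputation and no pooling is stated, so intervals for outcomes with missing survey answers would be too narrow

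*Protocol article*

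**What the plan says.** The Statistical Analysis section of the protocol article opens with a general commitment, "Missing values will be handled by imputation", and then names the technique: "Stochastic regression imputation with predictive mean matching as the imputation model will be used to prevent biased results based on complete case analysis only". The only purpose it gives is to avoid bias from a complete-case analysis. It states no number of completed data sets, no pooling rule and no adjustment to the standard errors.

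The same section then describes adherence and compliance as proportions and patient satisfaction as a multiple linear regression. For the economic evaluation it says "Bootstrap- and standard sensitivity analyses will be performed to quantify the uncertainty regarding the cost-effectiveness outcomes", without saying how the bootstrap relates to the imputation step.

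The Sample size section rests on precision alone. It expects "approximately 30% of women to have an elevated estimated risk of PE" and "an adherence of 70% and a compliance of approximately 40% is expected for the recommended aspirin treatment", turns these into "approximately 21% and 12% respectively of the general population", and concludes that to estimate them "with a precision of approximately 4% the required sample size is estimated at 400 participants".

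Non-response is foreseen. The Study Design and Recruitment section describes four web surveys, two automatic reminders, and a further step: "In case of non-response, women will be contacted by phone". No expected missing fraction is given.

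**The concern.** Adding a random residual or a donor draw to a regression prediction preserves the distribution of the variable, and so protects the point estimate better than filling in a mean. It does not make an imputed answer as informative as an observed one. If one completed data set is analysed in the usual way, the standard error is computed as though all the answers had been given. Two components of variance are lost: the smaller number of real observations, and the noise of the single random draw.

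This matters here because the sample size was chosen only to reach a given precision. If one completed file is analysed as observed, the reported half-width meets the planned 4 points however many answers were imputed. The study could then report its planned precision without having it.

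**Working it through.** **Inputs.** From the Sample size section: 30% at elevated risk, adherence 70%, compliance 40%, precision about 4 points, N=400. Assumed, because the article does not state them: a 95% confidence level and the missing fraction f, for which I use 5% to 30%. Also assumed: values missing completely at random, and no useful predictors in the imputation model.

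**Reproducing the plan's figure.** The two proportions are 0.30 × 0.70 = 0.21 and 0.30 × 0.40 = 0.12. With n = z²p(1-p)/d²:

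- p = 0.21, d = 0.04: 1.96² × 0.21 × 0.79 / 0.04² = 398.3, rounded up to 399, against 400 stated. The plan's figure reproduces.
- Half-width at n=400: 1.96 × √(0.21 × 0.79/400) = 3.99 points for 21%, and 1.96 × √(0.12 × 0.88/400) = 3.18 points for 12%.

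**Variance after one stochastic imputation.** The completed-data mean is (1-f) times the respondents' mean plus f times the mean of the imputed values. The respondents' mean has variance σ²/[n(1-f)]. Given the respondents, the random draws add f² × σ²/(nf) = fσ²/n. Hence

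true variance = (σ²/n) × [1/(1-f) + f], while the reported variance is about σ²/n.

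The ratio of true to reported standard error is √[1/(1-f) + f], and actual coverage of a nominal 95% interval is 2Φ(1.96/ratio) - 1. For example, at f = 20% the variance ratio is 1.25 + 0.20 = 1.45, the standard-error ratio is 1.204, the true half-width is 3.99 × 1.204 = 4.81 points, and coverage is 89.6%.

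**Simulation.** I checked the formula with 3,000 simulated data sets per setting at n=400, and compared it with multiple imputation (20 data sets, approximate Bayesian bootstrap draws, Rubin's rules). For p = 21%:

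| f | SE ratio | Reported half-width | True half-width, formula (simulation) | Coverage, formula (simulation) | Multiple imputation: half-width, coverage |
|---|---|---|---|---|---|
| 5% | 1.05 | 4.0 | 4.19 (4.18) | 93.8% (93.3%) | 4.1, 94.4% |
| 10% | 1.10 | 4.0 | 4.39 (4.41) | 92.5% (92.2%) | 4.2, 95.0% |
| 20% | 1.20 | 4.0 | 4.81 (4.83) | 89.6% (89.1%) | 4.5, 94.4% |
| 30% | 1.31 | 4.0 | 5.25 (5.26) | 86.4% (86.6%) | 4.8, 95.0% |

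With no missing values the two methods coincide (half-width 3.99 points). For p = 12% the simulated coverage of single imputation is 94.0%, 92.1%, 90.1% and 87.0% at the same four fractions, against 94.5% to 95.2% for multiple imputation.

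Two features are worth noting. The standard-error ratio depends on f but not on p or n, so to first order it also applies to the proportions in risk subgroups. And multiple imputation is better on both counts: its interval has the right coverage, and its half-width (4.8 points at f=30%) is smaller than the true one after single imputation (5.2-5.3 points), because averaging over data sets removes most of the noise of a single draw.

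**The case against.** **The article does not call the method single.** Predictive mean matching is also used inside multiple imputation, and a condensed article may leave the number of data sets and the pooling to a fuller plan. This stands to the extent that single imputation is the natural reading of the named method, not an explicit statement. It does not remove the point. The article fixes a method by name, and that name ordinarily denotes one draw per gap. Predictive mean matching settles how a value is drawn, not how many times.

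**The loss may be small.** Recommendations received, the basis for adherence, are asked in the first survey, sent at once after enrolment and followed by reminders and telephone contact. The prediction tool supplies 14 variables for nulliparous women and 6 more for multiparous women, and the surveys overlap in content, so imputation models need not be weak. This stands: at 5% to 10% missing, a correct half-width is 4.1 to 4.2 points, still close to the planned 4. It is less reassuring for compliance, which is asked in the postpartum survey.

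**The primary outcomes are descriptive.** The analysis section mentions no confidence intervals for adherence or compliance and states no test or threshold. That limits the consequences, but a study sized for precision will need to report it.

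**Stronger readings that the documents do not support.** A reader might infer that every confidence interval is too narrow; items with no missing answers are unaffected. A reader might infer that all outcomes depend on the surveys; the risk profile comes from the prediction tool, the Discussion says only that several outcomes rest solely on questionnaires, and it assigns the incidence of the neonatal composite to registry data. A reader might also infer that the cost-effectiveness uncertainty is certainly understated; the article does not say that one completed file is bootstrapped, and if imputation is repeated within each bootstrap sample the error does not arise.

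**Conclusion.** The point holds in a limited form. As named, and with no pooling or variance correction stated, the method understates uncertainty for outcomes with missing survey answers. At 5% to 30% missing, the standard error is too small by a factor of 1.05 to 1.31, and nominal 95% coverage falls to between about 93% and 87%.

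These sizes are conditional. The missing fraction is my assumption, the calculation takes values as missing completely at random with no useful predictors, and better predictors would shrink the loss. The point estimates of adherence and compliance are not threatened by this choice, and the effect on the cost-effectiveness results depends on an order of operations that the article leaves open. It should be corrected before analysis, but it does not undermine the study.

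**What to change.** Replace the named method with multiple imputation. Keep predictive mean matching as the draw method, but draw the regression parameters afresh for each data set. State the number of data sets (20 was enough in the check above) and pool estimates and standard errors by Rubin's rules. Include the prediction-tool variables and answers from the other surveys in the imputation models, since good predictors recover part of the lost precision.

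For the economic evaluation, state how imputation and bootstrap are combined: either impute within each bootstrap sample, or bootstrap within each imputed data set and pool.

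The cost is a change of wording, slightly more analysis work and computing time, and somewhat wider reported intervals (4.1 to 4.8 points instead of 4.0 for the 21% proportion, over the range assumed). No new data or participants are needed. With postpartum data collection planned to run until March 2019, the change could be made before analysis.

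### The economic horizon ends six weeks after birth, but the last survey follows the due date or a preterm redirect, so follow-up runs from about a day to 12 weeks; no quality-of-life measurement is listed before 24 weeks

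*Protocol article*

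**What the plan says.** The protocol article's Statistical Analysis section sets one horizon for the economic evaluation: "A time horizon of approximately eleven months, from onset of pregnancy up to six weeks post-partum, will be applied".

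Study Design and Recruitment sets the data collection. Women are asked to "complete 4 Web-based surveys at enrolment, 24 weeks and 34 weeks of gestation, and 6 weeks after due date". Enrolment is early, since one exclusion is "≥16 weeks of gestation at intake". The same section adds: "If women report PTB at the beginning of survey two or three, they will automatically be redirected to the postpartum survey".

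Data Collection gives the survey content. Four topics are listed for survey one: "The first survey addresses the following topics: (1) recommendations and information given by health care professionals, (2) women’s intention to comply with these recommendations", then diet and sunlight exposure, then supplement use. Neither quality of life nor resource use is among them. Surveys two and three add, among other topics, "3) maternal quality of life, (4) changes in vitamin and mineral supplement usage, and (5) health care resource use". Survey four repeats those topics and asks about care used by the newborn. On resource use, "information regarding the usage of health care resources will be requested at three intervals (surveys two, three and four) during the study period".

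Outcome Measures and Measurement uses these data in two cost-effectiveness ratios. One is per neonatal composite outcome prevented; that composite includes death within 7 days and neonatal intensive care admission within 28 days. The other is per maternal QALY. Statistical Analysis says that missing values will be imputed by stochastic regression with predictive mean matching.

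**The concern.** Six weeks after birth and six weeks after the due date coincide only for a birth at 40 weeks. The redirect widens the gap: a woman who has delivered preterm by survey two or three answers the postpartum survey then, and no later contact is described. The length of follow-up therefore depends on gestational age at birth, which the care paths may themselves change.

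For some preterm births the survey comes before the stated horizon ends, and even before the windows in the study's own composite close. Such a survey is complete, so nothing marks the later weeks as missing. Costs and events in those weeks would enter as zero.

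The start of the horizon raises a separate question for QALYs. They are to run from the beginning of pregnancy, but the first listed quality-of-life measurement is at 24 weeks. Early costs are a different matter, because survey two can collect them by recall.

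**Working it through.** **Inputs.** Surveys at 24 and 34 weeks and at six weeks after the due date, and the redirect (Study Design and Recruitment). Horizon to six weeks after birth (Statistical Analysis). Windows of 7 and 28 days (Outcome Measures and Measurement). Assumptions: due date at 40 weeks from the last menstrual period, and surveys answered on their scheduled date.

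**The plan's own figure.** 40 + 6 = 46 weeks = 322 days. 322 / (365.25/12) = 10.58 months, so approximately eleven months is a fair rounding for a birth at 40 weeks.

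**Weeks from birth to the last survey.**
- Birth after survey three: 46 − gestational age.
- Birth between surveys two and three, redirected at survey three: 34 − gestational age.

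| Birth (weeks+days) | Last survey at week | Weeks after birth | Difference from 6 |
|---|---|---|---|
| 24+1 | 34 | 9.9 | +3.9 |
| 28+0 | 34 | 6.0 | 0 |
| 30+0 | 34 | 4.0 | −2.0 |
| 31+6 | 34 | 2.1 | −3.9 |
| 33+0 | 34 | 1.0 | −5.0 |
| 33+6 | 34 | 0.1 (1 day) | −5.9 |
| 34+1 | 46 | 11.9 | +5.9 |
| 35+0 | 46 | 11.0 | +5.0 |
| 37+0 | 46 | 9.0 | +3.0 |
| 40+0 | 46 | 6.0 | 0 |
| 42+0 | 46 | 4.0 | −2.0 |

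Two births two days apart, either side of survey three, are followed for about 1 day and about 12 weeks. Two reminders at 6-day intervals could add up to 12 days (1.7 weeks), which moves the figures but does not remove the jump.

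**Composite windows.** 34 − 30 = 4 weeks = 28 days, so redirected births after 30 weeks are surveyed before the intensive care window closes. 34 − 33 = 1 week, so those after 33 weeks are surveyed before the 7-day death window closes.

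**QALY start.** 24 / 46 = 52% of the horizon has no listed measurement. The cohorts cannot differ through care before the risk assessment, which Table 1 places at 6-10 weeks. The unmeasured time in which care could matter is therefore 24 − 10 = 14 to 24 − 6 = 18 weeks, and about 24 − 16 = 8 weeks for intake close to the 16-week limit. The documents give no utility difference. For an assumed mean difference of 0.02 to 0.10, the unmeasured QALY difference per woman runs from 0.02 × 8 × 7/365.25 = 0.003 to 0.10 × 18 × 7/365.25 = 0.034.

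**The case against.** The case on the other side is that this concerns a secondary outcome and that several stronger readings fail. Most of that stands.

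- **Costliest births cut off.** A reader might infer that the earliest births lose their neonatal costs. The table shows otherwise: redirected births at 24 to 28 weeks are observed for 6 to 10 weeks. Only births at about 28 to 34 weeks fall short.
- **Savings understated.** This does not follow. Births at 34 to 39 weeks are observed beyond six weeks, so the net direction is mixed, and the documents give no effect on births at 28 to 34 weeks.
- **Scale.** The Discussion puts neonatal adverse events at about 5%, or 0.05 × 400 = 20 women. No count of redirected women is given; it is probably small.
- **Cancellation.** Data Collection says that survey intervals are similar in the two cohorts, so part of the error may cancel. It need not if gestational age at birth differs between them.
- **Registry.** The Discussion plans to study the incidence of the composite with regional registry data. That covers outcomes; registry costs are not mentioned.
- **The 52%.** This is a share of the horizon, not a size of bias, because the ratio uses differences between cohorts. Nor does the article say that costs over 46 weeks will be divided by QALYs over 22.
- **No baseline utility collected.** The text supports only that it is not listed. The survey topics may be condensed, the figure is not shown, and Statistical Analysis does not say which surveys carry the EQ-5D-3L.
- **Left to an analysis plan.** How utilities are interpolated commonly is. The conflict over when follow-up ends is different: both rules are stated in the article, and a plan for imputing missing values does not reach weeks that a completed survey hides.

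**Conclusion.** The concern holds in a limited form. The two sections disagree on when follow-up ends. The gap is −2 to +3 weeks at term, about +3 to +6 weeks for births at 34 to 36 weeks, and up to about 6 weeks short for births at about 28 to 34 weeks. Redirected births after 30 weeks are also seen for less than the 28-day intensive care window. As written, their later neonatal costs and events would be taken as zero.

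This rests on surveys answered on schedule and on no later contact with redirected women, since none is described. The effect on the cost-effectiveness ratios cannot be sized or signed from the documents.

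Separately, QALYs have no listed measurement for about 24 of 46 weeks. This concerns QALYs only. The primary outcomes, adherence and compliance, are not called into question by this point.

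**What to change.** Reconcile the survey schedule in Study Design and Recruitment with the horizon in Statistical Analysis, and apply the same rules to Expect I and Expect II:

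1. Compute costs and QALYs from the actual dates of birth and survey, standardised to six weeks after birth.
2. Where the postpartum survey precedes six weeks after birth, declare the remaining weeks of neonatal costs and outcomes missing. Impute them, or take the outcomes from the planned registry data, and add a sensitivity analysis.
3. Either state the maternal QALY over the observed window, from 24 weeks' gestation to the postpartum survey, or apply one common utility before 24 weeks in both cohorts and say that it contributes no difference.

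Do not rely on an extra survey in Expect II alone. Expect I closed inclusion at the end of 2015, and 300 of the 400 Expect II women were already enrolled, so a new contact in one cohort would weaken the similarity on which the comparison depends.

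The cost is a change of wording, somewhat more analysis work and, if the QALY starts at 24 weeks, a shorter stated QALY horizon.
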